## Abstract

**Background:**

Compared with open surgery, laparoscopic liver resection is a minimally invasive surgical technique. However, a number of patients experience moderate-to-severe postoperative pain after laparoscopic liver resection. This study aims to compare the postoperative analgesic effects of erector spinae plane block (ESPB) and quadratus lumborum block (QLB) in patients undergoing laparoscopic liver resection.

**Methods:**

One hundred and fourteen patients undergoing laparoscopic liver resection will be randomly allocated to three groups (control, ESPB, or QLB) in a 1:1:1 ratio. In the control group, participants will receive systemic analgesia consisting of regular NSAIDs and fentanyl-based patient-controlled analgesia (PCA) according to the institutional postoperative analgesia protocol. In the two experimental groups (ESPB or QLB group), the participants will receive preoperative bilateral ESPB or bilateral QLB in addition to systemic analgesia according to the institutional protocol. ESPB will be performed at the 8th thoracic vertebra level with ultrasound guidance before surgery. QLB will be performed in the supine position on the posterior plane of the quadratus lumborum with ultrasound guidance before surgery. The primary outcome is cumulative opioid consumption 24 h after surgery. Secondary outcomes are cumulative opioid consumption, pain severity, opioid-related adverse events, and block-related adverse events at predetermined time points (24, 48, and 72 h after surgery). Differences in plasma ropivacaine concentrations in the ESPB and QLB groups would be investigated, and the quality of postoperative recovery among the groups will be compared.

**Discussion:**

This study will reveal the usefulness of ESPB and QLB in terms of postoperative analgesic efficacy and safety in patients undergoing laparoscopic liver resection. Additionally, the study results will provide information on the analgesic superiority of ESPB versus QLB in the same population.

**Trial registration:**

Prospectively registered with the Clinical Research Information Service on August 3, 2022; KCT0007599.

## Administrative information

Note: the numbers in curly brackets in this protocol refer to SPIRIT checklist item numbers. The order of the items has been modified to group similar items (see http://www.equator-network.org/reporting-guidelines/spirit-2013-statement-defining-standard-protocol-items-for-clinical-trials/).

## Introduction

### Background and rationale {6a}

Laparoscopic liver resection is an increasingly common treatment option for the removal of benign masses or malignant tumors [1]. Laparoscopic liver resection has several advantages over open liver resection, including reduced pain and improved postoperative recovery [1–4]. However, a number of patients experience moderate-to-severe pain after laparoscopic liver resection [5]. For decades, opioids have been the mainstay of postoperative analgesia for this population. Although opioids provide excellent analgesia, opioid-related side effects, including nausea, vomiting, respiratory depression, and tolerance to analgesics are inevitably accompanied [6]. Reduced liver volume after liver resection can lead to delayed opioid metabolism and pronounced opioid-related side effects. Therefore, efforts should be made to reduce the opioid dose [7]. Recently, the Enhanced Recovery After Surgery (ERAS) Society recommended multimodal analgesia combined with intravenous (IV) opioids as the standard analgesia for laparoscopic liver resection [4]. Multimodal analgesia has been proposed to reduce opioid consumption while adequately addressing postoperative pain. It consists of several techniques and drugs with different mechanisms, including non-opioid analgesics (e.g., NSAIDs, acetaminophen), adjuvant anesthetics, and regional anesthesia [8]. Of these, regional anesthesia has emerged as a promising analgesic modality in this population [9], but relevant clinical data on analgesic efficacy and safety for each technique are lacking.

In our previous study comparing bilateral erector spinae muscle block (ESPB) with bilateral posterior quadratus lumborum block (QLB), we could not clearly demonstrate an analgesic difference between the groups [10]. This result may be attributed to the fact that we did not have a control group that received systemic analgesia alone or placebo. Another possible reason might be that the dose of local anesthetic (i.e., 40 mL of 0.375% ropivacaine) was too small to provide effective postoperative analgesia.

Therefore, in this study, we shall investigate the analgesic efficacy of ESPB or posterior QLB with 40 mL of 0.5% ropivacaine after laparoscopic liver resection compared with that in the control group. We will also measure chronological changes in plasma ropivacaine concentrations in both block groups to determine the safety of the local anesthetic dose in these patients. We hypothesize that ESPB or posterior QLB would reduce opioid consumption compared with conventional opioid-based analgesia in patients undergoing laparoscopic liver resection.

### Objectives {7}

We aim to evaluate the analgesic efficacy of the two interfascial blocks of ESPB and QLB in patients undergoing laparoscopic liver resection by comparing cumulative opioid consumption 24 h after surgery. We will investigate the differences in pain severity, cumulative opioid consumption, opioid-related side effects, and any block-related adverse events within 72 h after surgery among the groups. Postoperative recovery profiles will be also compared between the groups.

### Trial design {8}

This is a prospective, parallel-arm, double-blinded, superiority randomized controlled trial with 1:1:1 allocation.

## Methods: participants, interventions, and outcomes

### Study setting {9}

The present study will be conducted at Samsung Medical Center, a tertiary hospital located in Seoul, Republic of Korea.

### Eligibility criteria {10}

We shall enroll patients aged 19–69 years undergoing laparoscopic liver resection. The exclusion criteria are as follows: pregnancy, coagulopathy, cerebrovascular disease, systemic infection, inability to understand the study protocol, allergy to local anesthetics, psychopathy that may affect patient evaluation, and patient refusal.

### Who will take informed consent? {26a}

The research team members will invite eligible patients to participate in this study. The researchers (licensed medical doctors) will instruct them on the study protocol and obtain informed consent from all participants.

### Additional consent provisions for collection and use of participant data and biological specimens {26b}

Blood sampling will be performed only for 20 patients per group who receive ESPB or QLB at predetermined time points (30, 45, 60, and 240 min after administration of local anesthetics). The remaining blood samples will be discarded immediately after analysis of plasma ropivacaine concentration. We will obtain informed consent from all participants in advance.

## Interventions

### Explanation for the choice of comparators {6b}

The participants in the control group will be managed according to an institutional protocol.

The standardized anesthesia protocol is as follows: No premedication is given to any of the participants. Patient monitoring, including non-invasive blood pressure, EKG, pulse oximetry, and bispectral index (BIS), will be applied. After preoxygenation, general anesthesia will be induced with an IV injection of propofol (2 mg/kg) and rocuronium (0.8 mg/kg). After tracheal intubation, an arterial catheter is placed in the radial artery to continuously monitor blood pressure. Anesthesia is maintained with sevoflurane and IV infusion of remifentanil. The anesthetic concentration is adjusted to target BIS values of 40–50 and mean blood pressure and heart rate within 20% of the pre-induction values. IV hydromorphone (0.01 mg/kg) is injected 20 min before the end of surgery.

The standardized postoperative pain management protocol is as follows. After confirming full awakening from anesthesia, intravenous (IV) patient-controlled analgesia (PCA) is administered to the patient in the post-anesthesia care unit (PACU). The IV PCA consisting of fentanyl is programmed with a basal flow rate of 0.1 mL/h, bolus of 1 mL (15 μg), and a 15-min lockout interval. IV PCA is continued until postoperative day 3. In the ward, all patients are regularly administered IV ibuprofen 800 mg every 8 h. If patients present with breakthrough pain (NRS ≥ 4/10), IV hydromorphone (2 mg) is administered. Postoperative nausea and vomiting are treated with IV metoclopramide (10 mg).

### Intervention description {11a}

Except for the intervention of regional block and blood sampling for measuring plasma ropivacaine concentration, anesthesia, and postoperative pain management follow the same protocol as the control group. ESPB or QLB is performed after the induction of general anesthesia. These blocks will be performed by two experienced anesthesiologists ([name] and [name]). Intervention performers will not be involved in further data collection or outcome assessments. The procedure for each group is as follows:1. ESPB groupAll participants in the ESPB group will receive bilateral ESPBs in the right lateral decubitus position. After confirming the 8th thoracic vertebra by ultrasound, a 21-gauge, 100-mm echogenic needle (SonoPlex®, PAJUNK®, Geisingen, Germany) will be inserted into the transverse process of the 8th thoracic vertebra in the cranial-to-caudal direction under ultrasound guidance. Right ESPB will be performed first, followed by left ESPB. The spread of local anesthetic is confirmed by lifting the erector spinae muscle plane from the transverse process. A total of 40 mL of 0.5% ropivacaine (20 mL on each side) will be administered to each participant.2. QLB groupAll patients in the QLB group will receive bilateral QLBs in the supine position. After skin sterilization with 2% chlorhexidine, the same echogenic needle (SonoPlex®, PAJUNK®, Geisingen, Germany) will be inserted into the plane from the anterior-to-posterior direction and finally placed on the posterior surface of the quadratus lumborum under ultrasound guidance. The spread of local anesthetic is confirmed by pooling along the posterior aspect of the quadratus lumborum muscle. A total of 40 mL of 0.5% ropivacaine (20 mL on each side) will be administered to each participant.

In both the ESPB and QLB groups, blood samples will be collected from 20 patients in each group to determine plasma ropivacaine concentration. Through a pre-placed radial artery catheter, 5 mL of blood samples will be collected (i.e., a total of 20 mL) at predetermined time points (30 min, 45 min, 60 min, and 240 min after the end of both administrations of local anesthetics).

### Criteria for discontinuing or modifying allocated interventions {11b}

We will suspend the trial in cases of inappropriate spread of local anesthetic during ESPB or QLB, unexpected serious adverse events, and voluntary withdrawal of informed consent. These participants are considered as dropouts.

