### Sample size {14}

The sample size was calculated based on a previous study and the retrospective clinical data from our institution [5]. The mean cumulative opioid consumption during 24 h after laparoscopic liver resection was 45.5 mg with a standard deviation (SD) of 21.8 mg in IV morphine equivalent dose (MED) [12]. We hypothesized that bilateral ESPB and QLB will reduce cumulative opioid consumption by 30% compared with the control group. With an alpha of 0.05 and a beta of 0.8, 34 participants are required in each group using Dunnett’s test. Assuming a dropout rate of 10%, we plan to enroll 114 participants in the study. The sample size was calculated using the PASS 2021 (NCSS, LLC. Kaysville, UT, USA).

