### Implementation {16c}

The independent anesthetic nurse will open the sealed envelope of allocation information to confirm the assignment information on the operation day and prepare local anesthetics accordingly.

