### Methods in analysis to handle protocol non-adherence and any statistical methods to handle missing data {20c}

There will be no non-adherence issues in this study because the institutional standard protocol for postoperative pain management will be provided to all participants. The possibility of missing values in the primary outcome will be very low because data on opioid consumption will be collected using electronic medical records and PCA logs. Missing data will not be replaced.

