Our study has several limitations. First, the sham procedure is not used for participants in the control group. Second, the optimal dose of ropivacaine for ESPB or QLB has not been determined. Because ropivacaine is mainly eliminated by hepatic metabolism, delayed ropivacaine clearance in patients with liver disease may increase the risk of local anesthetic systemic toxicity (LAST), which may be aggravated after liver resection [26]. Based on our previous study [10], the peak plasma concentrations of ropivacaine were approximately 3-fold below the threshold for systemic toxicity after administration of 40 mL of 0.375% ropivacaine. Therefore, the 40 mL of 0.5% ropivacaine (approximately 15% increased dose) used in this study is not expected to reach the systemic toxicity threshold. Third, to ensure safety, only 20 participants from each block group will be tested for plasma ropivacaine concentration. The sample size of 20 may be too small to discriminate LAST between the groups. Fourth, we plan to measure total plasma ropivacaine concentrations. However, ropivacaine toxicity is dependent on unbound ropivacaine clearance, and the total plasma ropivacaine concentration alone may not be sufficient to determine systemic toxicity [27].

In summary, we anticipate that this trial will provide evidence for the efficacy and safety of ESPB and posterior QLB in patients undergoing laparoscopic liver resection. In addition, our data will provide clinical implications for determining the optimal dose of ropivacaine for ESPB and posterior QLB.

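### Randomised patients whose block spreads inappropriately become dropouts, which can happen only in the ESPB and QLB arms and probably removes them from the primary comparison

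*Protocol article*

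**What the plan says.** The section on discontinuing or modifying allocated interventions {11b} states: "We will suspend the trial in cases of inappropriate spread of local anesthetic during ESPB or QLB, unexpected serious adverse events, and voluntary withdrawal" of consent. It continues: "These participants are considered as dropouts". Although it speaks of suspending the trial, it evidently means the individual's participation.

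Three other places fix when and where the spread criterion can operate:

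- Implementation {16c}: an independent nurse "will open the sealed envelope of allocation information to confirm the assignment information on the operation day".
- Intervention description {11a}: "ESPB or QLB is performed after the induction of general anesthesia", and the operator checks the spread by ultrasound during the injection.
- Discussion, limitations: "the sham procedure is not used for participants in the control group".

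On handling in the analysis, the section on non-adherence and missing data {20c} says "There will be no non-adherence issues in this study" and "Missing data will not be replaced". It also says that opioid consumption comes from electronic medical records and PCA logs. Sample size {14} asks for 34 per group and enrols 114 to allow for 10% dropout. The article names no as-randomised analysis set.

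**The concern.** Inappropriate spread is a post-randomisation event that exists in two of the three arms. A control patient with the same anatomy has no block to fail and stays in. If dropouts are left out of the analysis, the block arms lose their failures and the control arm loses nobody.

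Two biases follow, both in favour of the blocks. First, failed blocks presumably work less well, so removing them inflates the estimated effect of being allocated to a block. Second, if poor spread occurs more often in patients who would need more opioid anyway, removing them creates a difference even when the blocks do nothing. Unequal failure between ESPB and QLB would also distort the pairwise comparison of the two blocks planned under additional analyses {20b}.

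The exclusion is also unnecessary, because the primary outcome can be recovered for these patients from the logs and records.

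The serious-adverse-event criterion is a separate and smaller matter. It applies to all three arms, but a patient made a dropout for this reason may contribute no 24–72 h outcomes to the analysed comparison.

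**Working it through.** **Inputs.** From Sample size {14}: control mean 45.5 mg, SD 21.8 mg (IV morphine equivalents), 30% reduction, alpha 0.05, 34 per group by Dunnett's test, 10% dropout, 114 in total. The stated beta of 0.8 is read as 80% power. From Statistical methods {20a}: two-sided testing. The documents give no block failure rate and no figure for the opioid use of patients with poor spread, so both are assumptions below.

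**1. The plan's own figures.** Target difference: 0.30 × 45.5 = 13.65 mg. For a two-sided Dunnett test of two block arms against control (simulated critical value about 2.24), the power to detect at least one difference is 0.787 at 34 per group and 0.800 at 35, so 34 is reproduced within tolerance. Dropout: 34 / 0.90 = 37.8, rounded up to 38; 38 × 3 = 114, exact. The calculation therefore expects 34 of 38 per arm to be analysed, which is the main evidence that dropouts are not analysed.

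**2. Where the rule acts.** The order is envelope opened, anaesthesia induced, block given, spread judged. The event is after allocation, and with no sham it has probability zero in the control arm. The 10% allowance is the same in every arm; this cause of dropout is not.

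**3. If the blocks work.** Let a fraction f of blocks fail and have no effect (assumption), with 38 randomised per arm. The as-randomised difference is 13.65 × (1 − f). With failures excluded it stays at 13.65 mg. The overstatement is 1/(1 − f) − 1.

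| f | As randomised (mg) | Failures excluded (mg) | Overstatement | Power, all analysed | Power, failures excluded (block n) |
|---|---|---|---|---|---|
| 5% | 12.97 | 13.65 | 5.3% | 0.793 | 0.822 (36) |
| 10% | 12.29 | 13.65 | 11.1% | 0.747 | 0.812 (34) |
| 15% | 11.60 | 13.65 | 17.6% | 0.697 | 0.802 (32) |

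Power is for at least one significant block arm.

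**4. If the blocks do nothing.** Let a fraction f of every arm be patients who would use g mg more than the rest, removed from the block arms only (assumption). The control mean is μ + f·g and the retained block mean is μ, so the spurious difference is f × g. Family-wise error was simulated with 38 per arm, SD 21.8 and Dunnett's critical value.

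| f | g (mg) | Spurious difference f × g (mg) | Family-wise error |
|---|---|---|---|
| 0 | – | 0 | 5.0% |
| 3% | 20 | 0.6 | about 5.2% |
| 5% | 10.9 (0.5 SD) | 0.55 | about 5.3% |
| 5% | 20 | 1.0 | about 5.5% |
| 10% | 10.9 (0.5 SD) | 1.1 | about 5.6% |
| 10% | 20 | 2.0 | about 7.0% |
| 10% | 30 | 3.0 | about 9.3% |

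Repeated runs differ by about 0.1 to 0.2 percentage points; the last row ranged from 9.2% to 9.4%.

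**The case against.** **Exclusion is inferred.** The dropout rule sits under discontinuation of interventions, the article defines no primary analysis set, and an analysis plan that is not shown may do so. The sentence on not replacing missing data concerns missing values; it does not by itself remove a patient whose opioid data exist. This stands as a limit on certainty. What remains is the word dropouts together with the enlargement from 34 to 38. An analysis plan that kept these patients would have to override the article's own rule.

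**The judgement precedes the outcome.** Spread is assessed against a stated ultrasound sign before any postoperative outcome exists, and the operators take no part in data collection or outcome assessment. This stands: it rules out exclusion driven by the outcome. It does not rule out selection on patient characteristics, nor does it make the criterion apply to controls.

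**The sizes are assumed.** Two experienced anaesthesiologists perform the blocks, and the 10% allowance covers every cause of dropout in every arm. An excess of 20–30 mg is 0.9–1.4 SD, and nothing in the documents links poor spread to higher opioid need. With a 0.5 SD excess the error rate barely moves. The null-case figures should be read as a range with an extreme top.

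**A tempting stronger reading on safety.** A reader might infer that toxicity cases are taken out of the safety data and that adverse-event rates in the block arms are therefore understated. The documents do not support this. No section removes a dropout's adverse events. Adverse event reporting {22} requires any serious adverse event to be reported, with no exception for dropouts. The criterion covers all arms and is limited to unexpected events, while the Discussion treats systemic toxicity as a foreseen risk.

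**A tempting contradiction.** A reader might also see a flat contradiction between {20c} and {11b}. The reason given in {20c} concerns postoperative pain management, not the technical success of a block. The adherence section {11c}, which mentions the single injection, comes closer. This is loose wording that needs aligning, not a second error.

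**Conclusion.** The point holds for the primary comparison. The article lays down a dropout reason that arises after randomisation and only in the block arms, and its sample size reasoning suggests that such patients are not analysed. In a superiority trial this replaces the randomised contrast with successful blocks against all controls.

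The direction favours the blocks, provided that a failed block works less well or that poor spread marks patients with higher opioid need. The size is illustrative. It is 0.7 to 2.1 mg on a true target of 13.65 mg if 5–15% of blocks fail and are inert. Under no effect it is about 0.6 to 3 mg, and most of the error inflation comes from the least plausible combinations.

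On safety, only a risk can be asserted: the 24–72 h outcomes of participants with unexpected serious adverse events may be lost from the analysed comparison. The rule should be corrected before the data are analysed.

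**What to change.** - Amend {11b} so that inappropriate spread or a serious adverse event ends neither follow-up nor inclusion in the analysis. Whether study procedures stop in such a patient is a clinical matter that this change leaves alone. Refer to the individual's participation, not to the trial.
- Analyse every randomised participant in the allocated group for 24 h opioid consumption, using PCA logs and electronic records. The only exception is withdrawal of consent for use of the data.
- Keep all randomised participants in the safety summaries.
- Report the analysis without failed blocks only as a labelled sensitivity analysis, with the number of failures per block arm.
- Reword {11c} and {20c} so that they acknowledge the failed blocks foreseen in {11b}.

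**Cost.** Recruitment began on 11 August 2022 according to Trial status, so this is a mid-trial amendment that needs Institutional Review Board approval and posting in the registry {25}. Follow-up of some existing dropouts may already have ended, although the logs and records may still supply their primary outcome. The estimated effect will be somewhat diluted: with 38 per arm, power for at least one significant block arm is about 0.83 with no failures and about 0.75 with 10% inert failures.
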